## Abstract

**Background:**

Trust in science and scientists has received renewed attention because of the “infodemic” occurring alongside COVID-19. A robust evidence basis shows that such trust is associated with belief in misinformation and willingness to engage in public and personal health behaviors. At the same time, trust and the associated construct of credibility are complex meta-cognitive concepts that often are oversimplified in quantitative research. The discussion of research often includes both normative language (what one ought to do based on a study’s findings) and cognitive language (what a study found), but these types of claims are very different, since normative claims make assumptions about people’s interests. Thus, this paper presents a protocol for a large randomized controlled trial to experimentally test whether some of the variability in trust in science and scientists and perceived message credibility is attributable to the use of normative language when sharing study findings in contrast to the use of cognitive language alone.

**Objective:**

The objective of this trial will be to examine if reading normative and cognitive claims about a scientific study, compared to cognitive claims alone, results in lower trust in science and scientists as well as lower perceived credibility of the scientist who conducted the study, perceived credibility of the research, trust in the scientific information on the post, and trust in scientific information coming from the author of the post.

**Methods:**

We will conduct a randomized controlled trial consisting of 2 parallel groups and a 1:1 allocation ratio. A sample of 1500 adults aged ≥18 years who represent the overall US population distribution by gender, race/ethnicity, and age will randomly be assigned to either an “intervention” arm (normative and cognitive claims) or a control arm (cognitive claims alone). In each arm, participants will view and verify their understanding of an ecologically valid claim or set of claims (ie, from a highly cited, published research study) designed to look like a social media post. Outcomes will be trust in science and scientists, the perceived credibility of the scientist who conducted the study, the perceived credibility of the research, trust in the scientific information on the post, and trust in scientific information coming from the author of the post. Analyses will incorporate 9 covariates.

**Conclusions:**

If there is a measurable effect attributable to the inclusion of normative language when writing about scientific findings, it should generate discussion about how such findings are presented and disseminated.

**Trial Registration:**

Open Science Framework n7yfc; https://osf.io/n7yfc

**International Registered Report Identifier (IRRID):**

PRR1-10.2196/41747

## Introduction

### Trust in Science and Scientists

The “infodemic” [1] accompanying the COVID-19 pandemic [2,3] has reinforced the importance of studying how people perceive information about and from scientific studies. When people are presented with a high volume of information of varying accuracy, we propose that there exists a broad social interest in *people making decisions based on the best available evidence*. Our team’s epistemological framework is that the scientific method is an excellent means of producing evidence. However, the suitability of the scientific method for producing knowledge, in general, does not necessarily mean that all purported scientific findings are of equal weight or that all scientists’ findings or statements are trustworthy [4,5]. Indeed, alongside truly remarkable scientific discoveries during the pandemic, Retraction Watch recently documented its 250th COVID-19 paper retraction, and many of the papers on their list are associated with commonly shared misinformation about the pandemic (eg, the supposed role of 5G networks in spreading COVID-19) [6]. Thus, although we will shortly argue that trust in science and scientists is valuable to understand, it is important not to conflate such trust with a more simplified aphorism such as “trust the science” [7], which (in our view, inappropriately) implies a singular “science” that is inherently worthy of trust.

At the same time, even though trust is defined and measured in a variety of different ways, studies conducted across multiple different populations have identified associations between trust in science and intention to get vaccinated or boosted for COVID-19 [8-12], as well as adherence to other measures to mitigate harm from the pandemic (eg, nonpharmaceutical interventions) [13-17]. Thus, even if the exact nature of the relationship is unclear, it is reasonable to speculate that trust in science and scientists is associated with people’s behaviors during a public health emergency such as COVID-19. We also note that trust in science and scientists is associated with belief in misinformation. Our research team has been studying trust in science and scientists as a complex and multifaceted variable using a conceptualization from Nadelson et al [18]. They validated a 21-item measure that includes multiple conceptual domains related to trust, computed using responses to items such as “We cannot trust scientists to consider ideas that contradict their own,” and “When scientists form a hypothesis they are just guessing” [18]. Using their 21-item measure to compute an aggregated value for trust, we found evidence of strong associations between low trust in science and belief in scientifically unsupported statements (eg, “misinformation”) about COVID-19 [19,20] and opioid overdose and naloxone [21].

We used those findings to develop a digital intervention, very deliberately rejecting approaches focused on the manipulation of trust in favor of creating truthful informational infographics to explain common misperceptions about science (ie, why it is appropriate for scientists to change their minds in response to new evidence) [22]. In a large preregistered, randomized controlled trial, we found evidence that 60 seconds of exposure to one such infographic, which featured an example of changing recommendations around butter and margarine, slightly and significantly increased trust in science and scientists and slightly reduced the likelihood that participants whose trust was thereby increased would endorse COVID-19 misinformation (ie, a mediational, but not direct, intervention effect) [20]. However, we observed no effects on behavioral intentions whatsoever, even though exploratory analyses showed that the trust variable remained associated with behavioral intentions [20].

This difference between the intervention’s effects on beliefs and behavioral intentions may raise questions about the ways in which scientific claims, as well as misinformation, may contain both cognitive and normative elements (which we unpack subsequently) and whether such elements are associated with trust in science and scientists. Furthermore, recent papers have reemphasized the importance of attending to both universals (eg, “trust in science and scientists”) and particulars (eg, “credibility of a specific scientist or claim”) in this area of study [4,5]. Thus, the remainder of this introduction makes the case for rigorously examining a seemingly small—but potentially important—distinction between cognitive and normative claims and the impact of such a difference on universal and particularized trust and describes our plan to do so.

### Cognitive and Normative Scientific Claims

In this study, we will scrutinize the differences between “cognitive” (ie, epistemic) claims of scientific findings and “normative” claims (ie, recommendations). For many scientific endeavors (such as experiments or evaluative studies), a key outcome of the research is 1 or more cognitive claims. A basic example of a cognitive claim is “the current is really strong out by the pier,” which is an assertion about the strength of the current. Importantly, a cognitive claim does not include a recommendation about what we ought to do if the claim is true. Such “ought” statements are instead normative claims, which pertain to what a person *should do* (eg, if it is the case that the current is really strong out by the pier, “...you should not swim there”) [23].

In a consequentialist account of rationality, cognitive claims can be separated from normative or practical claims [23]. We often use others’ cognitive claims to understand the world around us (eg, “we know by trusting what others tell us”) [24]. This trust is necessary because no person has the ability to generate empirical knowledge about everything (given constraints such as capacity, resources, interest, and time). Thus, people frequently make decisions about which and whose cognitive claims to trust [25].

In contrast, normative claims presume a framework of interests (eg, not wanting to swim in dangerous places), but such framing may not always apply to all persons (eg, someone who is at the pier to test a device built to measure current strength). Even if we trust a cognitive claim, we may not trust an associated recommendation [26]. A helpful real-life anecdote can be found in a headline from July 2021 titled “People are dressing in disguise for COVID-19 vaccines, Missouri doctor says” [27]. For the people in that story, the recommendation to get vaccinated was complicated, not because of any explicit disbelief in scientific cognitive claims about the vaccine, but because it did not account for a strong competing interest in not being “ridiculed” by friends, family, or coworkers. Similarly, when physical conflicts—including some resulting in death—erupted across the United States in 2021 over face masks, media coverage suggests the primary concern was not the science behind face masks, per se, but rather whether people *should* or *should not* be wearing them in a particular public space and time [28-31].

We hypothesize that some meaningful percentage of variability in trust in science and scientists, both generally and at the level of specific claims and persons, is attributable to the linguistic entanglement of cognitive and normative claims (eg, in press releases, popular summaries, and social media). In particular, we expect that some portion of mistrust is unrelated to scientific epistemic claims and may instead be explained by perceptions of discordant interests between laypersons and scientists. If that is the case, then we would expect to see reduced levels of trust and perceived credibility in study participants exposed to both a cognitive and normative claim about a study compared to those exposed only to a cognitive claim (ie, “I believe your finding, but I don’t agree with your recommendation”). If we are correct, it may have important ramifications for the way in which scientific findings are reported at multiple levels (eg, abstract, press release, news coverage, and social media).

### Study Objectives and Hypotheses

Our study will draw conclusions by randomizing a large, nationally representative sample of US adults to view a sample social media post that either (1) shares a cognitive claim from a 2020 study on face masks (control group), or (2) shares the same cognitive claim but also includes a normative claim about what people should do, given the cognitive claim, which is also from that study (intervention group; see Methods). We hypothesize the following (see Table 1):

Hypothesis 1: Overall trust in science and scientists (21-item scale) [18] will be significantly lower in the intervention arm (cognitive and normative claims) than the control arm (cognitive claim only).Hypotheses 2-5: The credibility of the scientist who conducted the study, credibility of the research, trust in the scientific information on the post, and trust in scientific information coming from the author of the post [32] will each be significantly lower in the intervention arm (cognitive and normative claims) than the control arm (cognitive claim only).Preregistered analyses (without hypotheses): We will study the interaction between the study arm and political orientation for each of the 5 preregistered hypotheses.

**Table 1 table1:** Design table.

Question	Hypothesis (if applicable)	Sampling plan (eg, power analysis)	Analysis plan	Interpretation given to different outcomes
What is the effect of intervention arm assignment on overall trust in science and scientists (21-item scale)?	Overall trust in science and scientists (21-item scale) will be significantly lower in the intervention arm than the control arm.	With 80% power (2-tailed test), this sample will allow us to detect small effects at α=.05 (Cohen *d*=0.14) and at corrected α=.01 (Cohen *d*=0.18) for differences between groups.	ANCOVA^a^, incorporating all 9 listed covariates	A significant effect will be interpreted as evidence that the inclusion of normative language caused the change (if the change exists), regardless of direction.
What is the effect of intervention arm assignment on the credibility of the research, credibility of the scientist who conducted the study, trust in scientific information from the author of the post, and trust in the scientific information on the post?	For hypotheses 2 through 5, each dependent variable will be significantly lower in the intervention arm than the control arm.	With 80% power (2-tailed test), this sample will allow us to detect very small effects at α=.05 (Cohen *d*=0.14) and at corrected α=.01 (Cohen *d*=0.18) for differences between groups.	ANCOVA, incorporating all 9 listed covariates	A significant effect will be interpreted as evidence that the inclusion of normative language caused the change (if the change exists), regardless of direction.
Are there any significant interactions between intervention arm assignment and political orientation on any of the prespecified dependent variables?	N/A^b^	N/A	Linear regression including the interaction between intervention arm and political orientation; the model will include the remaining 8 covariates	A significant interaction will be interpreted as possible evidence that political orientation may mediate or moderate the effect of including normative language in some way, regardless of direction, but that further research is needed.

^a^ANCOVA: analysis of covariance.

^b^N/A: not applicable.

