#### Participants and Procedures

This study will solicit participants (n=1500) from the Prolific crowdsourced US representative participant pool, which provides a cross-section of age, sex, and race/ethnicity that mirrors the national US population [34]. This sampling frame also provides the de facto eligibility criteria of being aged ≥18 years and residing in the United States. Studies have found the Prolific platform to produce high-quality research data in general and relative to competing services (eg, Qualtrics and Dynata panels, Amazon MTurk, and CloudResearch) [35,36].

When individuals indicate interest in participating in the study, they will be provided with a link to the experiment, which will be hosted on the QualtricsXM platform. Participants who agree to participate in the study (study information sheet) will complete the first block of questions, which will include sociodemographic items intermixed with screening questions to identify the risk of low-quality data (ie, virtual private network or bot use, inattention, and dishonesty) [37]. Individuals who fail 1 or more checks will be considered ineligible for the study and asked to return the study to the Prolific platform for reselection.

As noted in Figure 1, randomization will occur after all determinations of eligibility to preserve sample composition and allocation. The study will be fully insular (eg, all components occur within the QualtricsXM platform and within 1 “sitting”). To mitigate the potential impact of missing data, participants will not be permitted to advance the survey if they have not answered all questions on a given page. All data will be exported directly from the QualtricsXM platform to a local data file once the study closes, and the code used for data cleaning (see Sampling Plan) will be shared alongside the raw data.

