### Sampling Plan

#### Sample Size Determination and Power Analysis

As previously described, we will recruit 1500 individuals from the Prolific platform, with equal allocation to study arms. This sample size is currently the largest number of people for which the Prolific platform can assure national representativeness. We made the decision to recruit a large number of participants because we were unable to locate any baseline studies with which to estimate effect size, so we wanted to be conservative. In addition, although the issue of face masks continues to be a point of public contention, the prevalence of public health mandates related to face masks is lower than those in 2020-2021, which we suspect may serve to suppress the effect size relative to what it would be in the midst of more active social discord focused on that topic. With 80% power (2-tailed test), this sample will allow us to detect small effects at α=.05 (Cohen *d*=0.14) and at corrected α=.01 (Cohen *d*=0.18) for differences of trust in science between treatment and control. In keeping with modern inferential statistical recommendations, we will report all *P* values precisely rather than by threshold [40] and provide a balanced interpretation, especially where .01<*P*<.05.

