### Analysis Plan

#### Primary Outcomes

The primary outcomes are as follows.

Hypothesis 1Overall trust in science and scientists will be measured by the 21-item scale developed and validated by Nadelson et al [18]. An example item from the scale measures agreement with the statement, “When scientists change their mind about a scientific idea it diminishes my trust in their work.” This scale has demonstrated excellent internal reliability in our previous studies with crowdsourced samples (α>.900) [19-22,41].Hypotheses 2 through 5Single-item measures of credibility and trust that are specific to the hypothetical social media post and the scientist who conducted the study, from Song et al [32]“How credible is the scientist who conducted the study described in the post?” (1=not credible at all to 7=extremely credible); note that this language is slightly different than the original item to avoid ambiguity arising from the potential that a scientist authored the social media post“How credible is this research?” (1=not credible at all to 7=extremely credible)“I would trust scientific information if I knew it came from this author.” (1=strongly disagree to 7=strongly agree)“I trust this scientific information.” (1=strongly disagree to 7=strongly agree)

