#### Covariates

The covariates are as follows.

Familiarity with science will be measured by 1 item asking, “How often do you read science papers or science in the news?” (1=never to 5=always) [32]; this item was suggested in Song et al [32] as being potentially important to considerLevel of religious commitment (0=low to 10=high), as used in our previous studies [19,20,41]Political orientation (0=liberal to 10=conservative), as used in our previous studies [19,20,41]Political party (Republican, Democrat, or other), given recent research suggesting divergence between political orientation and party orientation pertaining to face masks [42]Race, ethnicity, gender, age (“About how old are you (*in years*)?”), and education level (“What is the highest grade or level of school you have completed, or the highest degree you have received?”) [43]

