#### Statistical Analyses

Descriptive statistics of demographics and outcomes will be calculated. We will explore distributions of trust in science (Hypothesis 1) and each of the single-item measures (Hypotheses 2-5).

Data will be analyzed using analysis of covariance (ANCOVA), with the assignment of the study arm (intervention vs control) used as the independent variable and the specified outcomes (depending on the hypothesis) set as the dependent variable. All specified covariates will be included in each model, and assumptions for the analyses will be evaluated (eg, the normality of residuals and linear relationships between covariates and the dependent variable). If assumptions are not met, the research team will explore different transformations or nonparametric models as recommended by statistical experts.

Missingness is not anticipated owing to the study design, but if it occurs at a meaningful level (>5%), we will perform sensitivity analysis using Multiple Imputation by Chained Equations to explore how missingness affects the results, and in the case that the results differ, we will report Multiple Imputation by Chained Equations as the primary analysis.

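### The arm-by-political-orientation interaction has no stated variance estimator and a fallback that would not keep the planned slope; prespecifying HC3 standard errors is a nearly free, low-severity improvement

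*Protocol article*

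**What the plan says.** The third row of Table 1 (Study Objectives and Hypotheses) sets the moderation analysis for all five outcomes: "Linear regression including the interaction between intervention arm and political orientation; the model will include the remaining 8 covariates". It does not say how standard errors will be computed. The hypothesis and sampling-plan cells of that row are marked not applicable. A significant result is to be read as possible evidence only, with further research needed.

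The moderator is "Political orientation (0=liberal to 10=conservative), as used in our previous studies" (Covariates). Four of the five outcomes are single 7-point items, two of them scored "1=not credible at all to 7=extremely credible" (Primary Outcomes). The sampling frame "provides a cross-section of age, sex, and race/ethnicity that mirrors the national US population" (Participants and Procedures); political orientation is not among the matched characteristics.

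Under Statistical Analyses, model assumptions are to be evaluated, with "the normality of residuals and linear relationships between covariates and the dependent variable" given as examples. If they fail, the team will explore transformations or nonparametric models on expert advice. The Trial Design section adds that analysts will know what the group variable means.

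**The concern.** The ordinary standard error of an interaction slope assumes the same residual variance at every level of the moderator. On a politically divided topic, people at one end of the scale may agree closely while those at the other end disagree among themselves. If the more variable end is also thinly populated, a few high-leverage participants carry much of the slope, and the ordinary standard error understates its uncertainty. Moderation by political orientation would then be declared too often, with intervals that are too narrow.

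The stated fallback does not repair this well. Transforming the outcome changes the scale on which the interaction is defined and can create or remove it. Standard rank-based two-group tests do not estimate how the arm effect changes along a 0 to 10 moderator. Either choice would be made after seeing the data, by analysts who know the arms.

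**Working it through.** **The plan's own figure.** The article gives "small effects at α=.05 (Cohen *d*=0.14) and at corrected α=.01 (Cohen *d*=0.18" for 80% power, two-sided, with 1500 people allocated equally (750 per arm). Detectable d = (z for alpha + z for power) × √(2/750):
- alpha .05: (1.960 + 0.842) × 0.05164 = 0.1447, which rounds to 0.14.
- alpha .01: (2.576 + 0.842) × 0.05164 = 0.1765, which rounds to 0.18.

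Both reproduce. They concern the main arm comparison and say nothing about the interaction.

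**Formula for the interaction.** Let x be orientation with mean μ, and s(x) the residual SD at x, the same in both arms. With 1:1 randomization the interaction is a difference between two slopes. The ratio of its true variance to the variance that ordinary regression reports is, in large samples,

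R = E[(x−μ)² s²(x)] / ( E[(x−μ)²] × E[s²(x)] ).

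The actual size of a nominal 5% test is 2 × (1 − Φ(1.96/√R)). R exceeds 1 only if the variance is larger where x is far from its mean, so spread that simply rises with x is not enough.

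**Assumed inputs (none is in the article).** SD linear in x, from 1 at x = 0 to 1.5, 2 or 3 at x = 10. Percentages of the sample at x = 0, 1, …, 10:
- mild liberal lean: 12, 11, 13, 12, 8, 13, 7, 8, 8, 4, 4 (mean 4.08)
- strong liberal lean: 18, 16, 15, 13, 8, 9, 6, 6, 5, 2, 2 (mean 3.18)
- conservative lean: the mild distribution reversed (mean 5.92)
- symmetric: uniform (mean 5)

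**One case in full** (strong lean, SD ratio 2): E[(x−μ)²] = 7.268, E[s²] = 1.810, E[(x−μ)² s²] = 17.506. R = 17.506 / (7.268 × 1.810) = 1.331. Then 1.96/√1.331 = 1.699, and the size is 8.9%. A correct interval would be √1.331 = 1.15 times as wide.

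**Size of the ordinary test at nominal 5%:**

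| Orientation | SD ratio 1.5 | SD ratio 2 | SD ratio 3 |
|---|---|---|---|
| Symmetric | 5.1% | 5.4% | 5.8% |
| Mild liberal lean | 6.1% | 7.0% | 8.3% |
| Strong liberal lean | 7.1% | 8.9% | 11.6% |
| Conservative lean | 4.4% | 4.1% | 4.0% |

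If spread instead falls with conservatism (SD ratio 0.5), the directions reverse: 4.1% and 3.1% for the mild and strong liberal leans, 7.0% for the conservative lean.

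**Simulation** (N = 1500, 1:1, no true interaction). With seven further covariates and an SD ratio of 2, the ordinary test rejected 5.1% (uniform), 6.8% (mild liberal lean) and 8.8% (strong liberal lean). A separate simulation put the conservative-lean case at 3.4% to 4.6%. HC3 rejected 4.5% to 5.6% in every normal-error setting of the main simulation, and about 4% to 6% in the separate one.

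**Role of the 7-point cap.** With constant latent SD and a mean that falls with conservatism, the cap alone gave 4.5% to 6.1% for the ordinary test and 4.5% to 5.2% for HC3. For rounded 1 to 7 items in a strongly liberal-leaning sample, the ordinary test rejected 5.1% with constant latent SD and 7.3% with a latent SD ratio of 1.5. The cap by itself does little.

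**Power.** With constant variance, power was 86.8% with ordinary errors and 86.6% with HC3. With the SD doubling in a strongly liberal-leaning sample, HC3 brought the size from 8.8% to 5.1%, and the rejection rate under a true interaction went from 82% to 75%.

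**The case against.** The strongest reply is that the article does not commit to ordinary standard errors. Linear regression is compatible with robust errors, and the choice of variance estimator is often left to a fuller analysis plan. The assumption checks are introduced as examples, so a check of constant variance is not excluded. The analysis carries no hypothesis and no power target, and its interpretation is already cautious. All of this stands, and it is why the point ranks low.

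A reader might go further and infer that the plan checks only normality and linearity, or that spread growing with conservatism is enough to produce false moderation. The documents support neither. The list of checks is illustrative. Growing spread without skew leaves the test near 5%, and in a conservative-leaning sample the test becomes conservative. Matching on age, sex and race/ethnicity leaves orientation uncontrolled but does not imply a liberal lean.

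It is also too strong to say that HC3 costs nothing. Where ordinary errors are too small, rejections under a true interaction fall as well (82% to 75% in the example). That is the price of a valid test.

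What survives is the fallback. The only remedies that the article names would alter or lose the planned slope, and they are chosen after the data are seen. HC3 keeps the same model and the same estimand.

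**Conclusion.** The point holds as a low-severity improvement. Under the default reading, the size of the interaction test depends on two quantities that the article does not give: the skew of political orientation and the trend in residual spread across it. For SD ratios of 1.5 to 2 with spread rising toward the conservative end, size is roughly 6% to 9% with a liberal-leaning sample, about 5% with a symmetric one, and about 3.5% to 4.5% with a conservative-leaning one. In the liberal-leaning cases correct intervals would be about 4% to 15% wider than those reported (√1.091 = 1.04 to √1.331 = 1.15). These figures assume equal variance patterns in the two arms.

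A reader might infer that the trial's main conclusions are at risk. They are not: with 1:1 allocation the ordinary standard error of the arm comparison stays close to correct, and simulated rejection rates for it were 4.9% to 5.5% with either type of standard error.

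**What to change.** Add to the third row of Table 1 and to Statistical Analyses: 'Arm-by-political-orientation interactions will be tested, and their confidence intervals computed, with heteroskedasticity-consistent (HC3) standard errors, regardless of the result of any check of constant variance.' Making it unconditional removes a data-dependent choice. Also state that transformations or nonparametric models, if explored for the interaction, are sensitivity analyses that do not replace this estimate. The same option may be used for the Hypothesis 1 to 5 models, where it changes almost nothing.

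The cost is one or two sentences and one software option. It needs no extra participants or data and loses negligible power if variance is constant.

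### Table 1 allows a significant arm-by-political-orientation interaction to be read as possible mediation, but the planned model can support moderation only

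*Protocol article*

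**What the plan says.** Under Study Objectives and Hypotheses, the protocol article announces a set of analyses that are preregistered but carry no hypotheses: "We will study the interaction between the study arm and political orientation for each of the 5 preregistered hypotheses". The third row of Table 1 gives the model: "Linear regression including the interaction between intervention arm and political orientation; the model will include the remaining 8 covariates". The last column of that row, which fixes the interpretation of each possible result, takes a significant interaction as possible evidence that "political orientation may mediate or moderate the effect of including normative language in some way". The sentence then continues with a qualification: "regardless of direction, but that further research is needed". The hypothesis and sampling-plan cells of the row are marked as not applicable.

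The Covariates section lists the variable with the other adjustment variables: "Political orientation (0=liberal to 10=conservative), as used in our previous studies". It is one of the nine covariates entered in every ANCOVA for Hypotheses 1 to 5.

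On timing, Participants and Procedures says that consenting participants "will complete the first block of questions, which will include sociodemographic items intermixed with screening questions", and that randomization comes after eligibility has been settled. Political orientation is not named there, and the workflow figure is not available in the text reviewed.

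**The concern.** Mediation and moderation are different causal claims. A mediator is changed by the assigned exposure and passes some of the effect on to the outcome. A moderator is a characteristic across whose levels the effect differs. The interpretation cell offers both as readings of one test result, and the test addresses only the second.

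The cell matters because it is a rule for drawing conclusions, fixed in advance and applied to five outcomes. A report that followed it could cite a preregistered basis for suggesting that normative language works by shifting readers' political orientation. Nothing in the planned analysis would bear that out.

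**Working it through.** The plan states no figure on this point, so there is none to reproduce. The check is of the model against the two claims.

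**Inputs from the protocol article**
- Model: linear regression of each outcome on arm, political orientation, their product and the other eight covariates (Table 1, third row).
- Role of orientation: covariate, scored 0 to 10 (Covariates).
- Timing: background items in a first block, randomization after eligibility (Participants and Procedures). That orientation belongs to this block is an inference.
- Design: two parallel groups, 1:1, 1500 participants, so 750 per arm (Trial Design; Sample Size Determination and Power Analysis).

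**Step 1. What the planned model estimates.** Let A be the arm (0 or 1), M political orientation and Y the outcome:

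Y = b0 + b1·A + b2·M + b3·A·M + other covariates + error.

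The arm effect at orientation m is b1 + b3·m. Testing b3 = 0 asks whether that effect changes with m. This is moderation.

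**Step 2. What mediation would need.** A second model is required: M = a0 + a1·A + error. In linear models without a product term, the indirect effect is a1·b2. With the product term it is a1·(b2 + b3·a), evaluated at arm a. Both expressions contain a1 as a factor. If a1 = 0, the indirect effect is zero whatever b3 is. The plan estimates b3 but never a1.

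**Step 3. What a1 is here.** If orientation is recorded before allocation, the post cannot alter it, and a1 = 0 by design. If it were recorded afterwards, a1 could differ from zero, but the plan would still contain no estimate of it and no indirect effect. In neither case does a significant b3 support mediation.

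**Step 4. Illustration.** A simulation used n = 1500 (750 per arm), 2000 replicates, ordinary least squares of Y on A, M and A·M, and alpha .05. M and the errors had SD 1, and the coefficient of M was 0.3. All effects are assumed and none comes from the documents.

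| Scenario | Interaction significant | Arm-to-M path significant |
|---|---|---|
| No arm effect of any kind | 5.4% | 4.9% |
| Moderation only (b3 = −0.2) | 97.4% | 5.2% |
| Mediation only (a1 = 0.3, b3 = 0) | 5.1% | 100% |

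The 5.1% in the last row follows from setting b3 to zero, so the table illustrates steps 1 to 3 and is not independent evidence. It shows that a significant interaction can occur with no arm-to-M path, and that such a path can exist with the interaction test at chance level.

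**Step 5. The article's own usage.** In the introduction, under Trust in Science and Scientists, the authors describe an earlier trial's effect as mediational where it ran through trust that the intervention had raised. That is the standard meaning. The Table 1 cell departs from it.

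**The case against.** The best defence is that the sentence is tentative and the analysis secondary. The rule speaks only of possible evidence, offers moderation as an alternative, and ends with a call for more research. The analyses carry no hypotheses, and neither Expected Findings nor Next Steps mentions political orientation. The question, the stated aim and the model in that row all specify an interaction, which is the right tool for moderation. The phrase may simply be loose. All of this stands, and it limits the severity. It does not rescue the word: hedging suits weak evidence, and a significant interaction by itself is not evidence of mediation at all.

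Three stronger readings are tempting, and the documents do not support them.

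- A reader might infer that the ANCOVAs for Hypotheses 1 to 5 adjust for a mediator and are therefore biased. That would follow only if the post changed orientation. The article never says that it does, and the natural reading of Covariates with Participants and Procedures is that orientation is a background item collected before exposure. On that reading the adjustment is sound.
- A reader might infer that the plan commits to a claim about mechanism. It does not, given the either-or wording and the caveat.
- A reader might say that an interaction coefficient never carries information about mediation. As a general statement this is too absolute: where the exposure does change the mediator, b3 enters the indirect effect (step 2). The narrower statement is enough here: without an arm-to-orientation path, a significant b3 says nothing in favour of mediation.

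**Conclusion.** Wrong as written, low severity. The planned product-term regression can support the statement that the arm effect differs by political orientation. It cannot support the statement that orientation mediates the effect. The error affects the permitted wording of five secondary interaction analyses. No estimate, test, alpha level or sample size changes, and the conclusions on Hypotheses 1 to 5 are untouched.

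That orientation precedes randomization is inferred, because the article does not place the item explicitly. The verdict does not depend on this, since the plan contains no indirect-effect analysis under either timing.

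**What to change.** In the third row of Table 1, delete the words *mediate or* and word the rule so that a significant interaction is possible evidence that the arm effect differs by political orientation. Keep the existing caveat about further research.

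Two optional clarifications would help: that political orientation is recorded before randomization, if that is the case, and that orientation is not itself randomized, so an observed difference in the arm effect may reflect traits correlated with it.

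The cost is one wording change. No new data, model or analysis is needed.
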